## SWOG S1200 SUPPLEMENTAL AGENTS REPORTING FORM

SWOG Patient ID      

SWOG Study No. S  1  2  0  0

Registration Step  1

Patient Initials \_\_\_\_\_ (L, F M)

**Reporting period** (select one): ☐ Baseline ☐ Registration to 1-week visit ☐ 1-week visit to 3-week visit  
☐ 3-week visit to 6-week visit ☐ 6-week visit to 12-week visit ☐ 12-week visit to 16-week contact  
☐ 16-week contact to 20-week contact ☐ 20-week contact to 24-week visit ☐ 24-week visit to 52-week visit

### Other Medications:

Please list any of the following other medications taken during the reporting period. Indicate dosage and frequency using the frequency codes below.

|                                                          | Dosage                                                                       | Frequency     |
|----------------------------------------------------------|-------------------------------------------------------------------------------------|----------------------|
|  Statins (e.g., Lipitor)         |     |  |
|  Aspirin                         |     |  |
|  Bisphosphonates, specify: _____ |     |  |

### Frequency codes:

1 = ≤ once per week  
2 = 2-3 times per week  
3 = 4-6 times per week  
4 = once a day  
5 = more than once a day

### Steroids:

Please list all steroids taken during the reporting period. Indicate dosage and frequency using the frequency codes below.

|                                                           | Dosage                                                                       | Frequency     |
|-----------------------------------------------------------|-------------------------------------------------------------------------------------|----------------------|
|  Steroid pills
Type: _____     |     |  |
|  Steroid injection
Type: _____ |     |  |
|  Steroid cream
Type: _____     |                                                                                     |  |

### Frequency codes:

1 = ≤ once per week  
2 = 2-3 times per week  
3 = 4-6 times per week  
4 = once a day  
5 = more than once a day

Has the patient used therapeutic massage for joint symptoms since the last assessment? ☐ Yes ☐ No

Has the patient used any dietary supplement for joint symptoms since the last assessment? ☐ Yes ☐ No

### Comments:

[figure not shown]

**DRAFT****SWOG  
S1200 ASSESSMENT OF BLINDING**

Page 1 of 1

SWOG Patient ID  SWOG Study No. S1200 Registration Step 1

Patient Initials \_\_\_\_\_ (L, F M)

Date of Completion:  /  / **Planned assessment:** ☐ 6-week visit ☐ 12-week visit ☐ 24-week visit ☐ 52-week visit**Instructions:** You will be asked to complete this form at 6 weeks, 12 weeks, 24 weeks and 52 weeks post-registration. Thank you for your participation on this study.**1. Do you think you were receiving true acupuncture during your study participation?**☐ Yes ☐ No ☐ Not applicable (Waitlist control arm)**2. Did you get any acupuncture treatments outside of this clinical study?**☐ Yes ☐ No**If Yes, how many acupuncture treatments did you receive in the past 6 months outside of this clinical study?** [figure not shown]

**DRAFT****SWOG  
S1200 OFF PROTOCOL NOTICE**

Page 1 of 1

SWOG Patient ID 

SWOG Study No. S1200

Registration Step 1

Patient Initials \_\_\_\_\_ (L, F M)

Institution / Affiliate \_\_\_\_\_ Physician \_\_\_\_\_

**Instructions:** Submit this form within 2 weeks after completion (or discontinuation) of study intervention.All dates are **MONTH, DAY, YEAR**. Explain any blank fields or blank dates in the **Comments** section.Place an ☒ in appropriate boxes.**Off Protocol Reason** (select one):

- ☐ Completion of 12 weeks of study intervention
- ☐ Medically required, specify: \_\_\_\_\_
- ☐ Patient refused, logistics (e.g., transportation) or scheduling conflicts, specify: \_\_\_\_\_
- ☐ Patient refused, other reason, specify: \_\_\_\_\_
- ☐ Evidence of any cancer, specify: \_\_\_\_\_
- ☐ Death (submit Notice of Death form)
- ☐ Other, specify: \_\_\_\_\_

**Off Protocol Date**Date of completion, evidence of cancer, death or decision to discontinue therapy:  /  / Date of Last Contact or Death:  /  / Vital Status: ☐ Alive ☐ Dead (submit Notice of Death form)**Comments:**[figure not shown]

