#### 7.6 Acupuncture Treatment

##### a. Acupuncture Schedule

Patients will be randomized (2:1:1) to true acupuncture vs. sham acupuncture vs. waitlist control. Patients will be blinded to true acupuncture vs. sham acupuncture. Patients will not be blinded to the waitlist control. The study intervention is to begin within 5 working days of registration.

- True acupuncture administered twice weekly for 6 weeks followed by weekly treatments for 6 weeks (12-18 sessions total over 12 weeks).
- Sham acupuncture administered twice weekly for 6 weeks followed by weekly treatments for 6 weeks (12-18 sessions total over 12 weeks).
- Duration of intervention – Study intervention will be continued for 12 weeks unless unacceptable toxicity occurs, the subject has concurrent illness that necessitates withdrawal or subject decides to withdraw from participation for any reason. If the subject’s medical condition is influenced by the knowledge of which study intervention she was assigned, there will be unblinding upon the Investigator’s request.

- A licensed Study Acupuncturist(s) designated at each site will administer the true and sham acupuncture treatments.
- After the 24-week visit, all patients will receive a voucher for 10 free true acupuncture sessions administered by the Study Acupuncturist(s) and to be used at the patient's convenience and documented in the web-based calendar.

During the first 6 weeks of acupuncture, the twice weekly acupuncture sessions should be at least 24 hours apart and if a session is missed, it may be made up the following week for up to 3 sessions per week. The schedule will be flexible to allow for 8-12 sessions during the first 6 weeks, which may be more reflective of what may happen in the "real world" setting. During the second 6 weeks of weekly maintenance acupuncture, there will be no make-up of missed sessions, so patients may have only 1 session per week during the second 6 weeks of the study intervention (Week 7 to 12). Breaks of up to 30 consecutive days are allowed.

b. Documentation of Acupuncture Visits

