# +/- 3 days to allow flexibility in scheduling of assessments.

^ +/- 7 days to allow flexibility in scheduling of assessments.

$\pi$  After the Week 24 visit, all patients will receive a voucher for 10 free true acupuncture sessions to be administered by the study acupuncturist(s) and used off-study at her convenience.

\* True/Sham acupuncture will be administered twice weekly for 6 weeks (12 sessions) followed by 6 weekly treatments (6 sessions) of maintenance (18 sessions total over 12 weeks).

% Patients on the Waitlist Control arm will not receive any acupuncture (true or sham) until given the vouchers at Week 24. All forms must be submitted as required in Section 14.0.

† Telephone contact at Weeks 2 and 4 will include assessment at adherence to acupuncture, use of pain medications, and adverse events.

~ Telephone contact at Weeks 16 and 20 will include phone administration of the **S1200** Brief Pain Inventory - Short Form (Form #40963) and assessment of use of pain medications.

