Acupuncture needles used will be Mac™ single-use, sterile, and disposable. The full body acupuncture needles will be 1 inch, 1.5 inches or 3 inches and 34-gauge (manufactured by Tian Jin Haing Lin Sou Won Medical Instrument Co., Ltd; distributed by Mac Co., Roslyn Heights, New York, USA) and auricular needles will be 15mm and 38-gauge (Seirin-America, Inc., MA). The needling protocol will consist of first swabbing all points with alcohol and needling auricular points, then needling full-body points. The needles will be inserted to the proper needling depth as determined by standard point locations and to elicit a *de qi* sensation at all standardized full body acupuncture points. (152) The needles will remain *in situ* for 20-25 minutes during which the Study Acupuncturist will return to stimulate the needles once, utilizing even needle technique in order to re-elicited the *de qi* sensation. If needed, to access joint-specific points that are not accessible in the supine position, needles may be inserted after the first set, at the proper depth and angle, eliciting a *de qi* sensation, and retained for 10 minutes. No electrical stimulation will be used. One licensed Study Acupuncturist will perform all treatments. In addition, up to 2 licensed acupuncturists will be trained in administering the protocol in the event of schedule conflicts. At 6, 12, 24, and 52 weeks, to assess the adequacy of blinding, patients will give an opinion about their treatment assignment. After the 24-week visit, patients will receive a voucher for 10 free acupuncture sessions to be administered by the study acupuncturist(s) used off-study at her convenience. Any additional acupuncture treatments received off-study will be recorded at 24 and 52 weeks. All of this information will be recorded on the **S1200** Assessment of Blinding Form (Form #20574).

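### The six-month recall on Form #20574 misses about the first two weeks after voucher issue at Week 52, and its wording leaves unclear whether voucher sessions count

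*Protocol*

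**What the plan says.** Protocol Section 10.2 states that use of additional off-study acupuncture will be assessed. The instrument is Form #20574. Its instruction reads "You will be asked to complete this form at 6 weeks, 12 weeks, 24 weeks and 52 weeks post-registration", and Section 14.7 requires it at the same four visits. Item 2 opens with a yes/no question that has no time limit, "Did you get any acupuncture treatments outside of this clinical study". A woman who answers yes is then asked "how many acupuncture treatments did you receive in the past 6 months outside of this clinical study". The wording is the same at every visit.

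The text of Section 19.1 is narrower on timing: "Any additional acupuncture treatments received off-study will be recorded at 24 and 52 weeks".

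On the vouchers, the Section 9.0 footnote says "After the Week 24 visit, all patients will receive a voucher for 10 free true acupuncture sessions". It labels these sessions off-study, although the study's own acupuncturist gives them. Section 7.6a adds that they are "to be used at the patient's convenience and documented in the web-based calendar".

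**The concern.** A recall item gives a complete count only if its look-back reaches the previous completion of the form or the start of the exposure. Here the look-back is fixed at six months while the visit intervals are 6, 6, 12 and 28 weeks. The last interval is longer than the look-back. The uncovered stretch comes immediately after all three arms receive ten free sessions of the active treatment.

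The wording raises a second problem. The term off-study, which the protocol uses for voucher sessions, does not appear on the patient's form. She sees a question about acupuncture outside the clinical study, just below one about her study participation, while she is still in follow-up and may be attending the study acupuncturist on a study voucher. Women may reasonably answer in different ways.

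At stake is the description of true acupuncture received after Week 24, including in the sham and waitlist arms. That description is needed to interpret the Week 52 results, which Section 1.2 presents as the long-term evaluation and Section 2.0 as durability 40 weeks after stopping.

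**Working it through.** The protocol gives no figure to reproduce. The check is interval arithmetic.

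**Inputs**
- Look-back L: six months (Form #20574, item 2). L = 365.25 / 2 / 7 = 26.09 weeks.
- Form visits: Weeks 6, 12, 24 and 52 from registration (the form; Section 14.7).
- Vouchers: issued after the Week 24 visit (Sections 7.6a and 9.0).
- Visit windows: 7 days either way at Weeks 24 and 52 (Section 9.0).
- Prior acupuncture: excluded in the 12 months before registration (criterion 5.7).

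**Step 1: recall window at each visit, from v − L to v, in weeks from registration**

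| Visit | Window |
|---|---|
| Week 6 | −20.1 to 6 |
| Week 12 | −14.1 to 12 |
| Week 24 | −2.1 to 24 |
| Week 52 | 25.9 to 52 |

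**Step 2: uncovered time after Week 24.** Gap = max(0, Week 52 date − L − Week 24 date).
- Nominal dates: 52 − 26.09 − 24 = 1.91 weeks, or 1.91 / 28 = 7% of the interval.
- Shortest interval (Weeks 25 and 51): 51 − 26.09 − 25 = −0.09, so no gap.
- Longest interval (Weeks 23 and 53): 53 − 26.09 − 23 = 3.91 weeks, or 3.91 / 30 = 13%.
- If a patient takes six months to mean 24 weeks, the nominal gap is 52 − 24 − 24 = 4 weeks.

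**Step 3: overlap before Week 24.** A session in weeks 0–6 lies in three windows (Weeks 6, 12 and 24), one in weeks 6–12 lies in two, and one in weeks 12–24 lies in one. The Week 24 window reaches back past registration, so the Week 24 answer alone covers weeks 0–24. The Week 52 window does not overlap it.

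**Step 4: which record holds voucher sessions.** Section 7.6a puts them in the web-based calendar. Sections 7.3b and 19.1 name Form #20574 as the record of additional acupuncture. The Adherence to Acupuncture form (#6044), which is the listed route by which calendar data are submitted, is due only up to Week 12 (Section 14.7), and its last period is weeks 6–12. No form in Section 14.0 carries calendar sessions after Week 24 into the submitted data, and no rule says which source prevails.

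**Step 5: effect of the change.** Asking for sessions since the previous completion of the form gives windows 0–6, 6–12, 12–24 and 24–52, with no gap and no overlap.

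**The case against.** The strongest objection is that the trial has a second record. Voucher sessions go into the web-based calendar, which has no six-month limit, so early voucher use missing from the form need not be missing from the trial. This stands. A reader might infer that the form is the only information on extra acupuncture, or that the trial loses 2 to 4 of a woman's 10 voucher sessions, and up to 8 at the widest visit spacing. The documents do not support either. Those session counts assume that use starts on the day of the visit and runs weekly or twice weekly, whereas the protocol leaves the pace to the patient. They describe what the form omits, not what the trial omits. The objection does not remove the point, because no listed form brings the calendar's voucher sessions into the submitted data and no reconciliation rule is given. Nor does the protocol describe calendar entries for acupuncture from other practitioners.

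A reader might also infer that sessions before Week 24 are counted two or three times. That would happen only if counts were added across visits, and the protocol plans no such sum. The Week 24 count is complete on its own, and criterion 5.7 should leave its short pre-registration part empty.

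A third objection is that voucher sessions are called off-study throughout, so the item literally includes them. That is a fair reading for someone holding the protocol, but the patient has only the form. How many women would misread it is unknown.

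Finally, the yes/no question has no time limit, so a woman whose only use fell in the gap can still answer yes at Week 52. Any-use status is therefore preserved. The number of sessions is not.

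**Conclusion.** The point holds in a limited form. As written, the Week 52 count omits about 1.9 weeks directly after voucher issue on nominal dates (0 to 3.9 weeks across the visit windows), and it is ambiguous for voucher sessions. The ambiguity may matter more than the gap, because it can affect the whole Week 52 count.

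The size rests on reading six months as 26.1 weeks and on patients applying that limit literally, which real recall only approximates. Whether under-counting would differ by arm, for example because waitlist women use vouchers sooner, is plausible but not shown by anything in the documents.

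The consequence is confined to the descriptive assessment in Section 10.2 and to interpreting Week 52, which Section 2.0 classes as a secondary exploratory endpoint. The primary endpoint is untouched, since the Week 6 window covers all of weeks 0–6. Week 24 is untouched, since its window is complete and vouchers come afterwards. No power or alpha figure depends on this item. The priority is low.

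**What to change.** On Form #20574, item 2:
- Replace the six-month look-back with since the last assessment, the style already used on the Supplemental Agents form (#9413), and since registration at Week 6. Name the visit at which this form was last completed, so that the telephone contacts at Weeks 16 and 20 are not taken as the starting point at Week 24.
- At Week 52, ask for two counts since the Week 24 visit: sessions taken with the study voucher, and any other acupuncture.

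In the protocol, state that voucher counts are taken from the web-based calendar and that the form is used for non-voucher sessions. The patient's own voucher count then serves as a check.

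The cost is one reworded item and one extra number field on a form still marked as a draft, with no added contact. The small downside is a recall period of about 28 weeks instead of 26 at Week 52.

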# SWOG FOLLOW UP FORM

Page 1 of 1

SWOG Patient ID SWOG Study No. S Registration Step 

Patient Initials \_\_\_\_\_ (L, F M)

Institution / Affiliate \_\_\_\_\_ Physician \_\_\_\_\_

Participating Group: Group Name/Study No./Patient ID \_\_\_\_\_ / \_\_\_\_\_ / \_\_\_\_\_

**Instructions:** Please submit at each follow up after completion of treatment until relapse or progression, at time of relapse or progression, and at protocol-specified intervals after relapse or progression. Also submit at time of diagnosis of second primary. All dates are **MONTH, DAY, YEAR**. Answer all questions and explain any blank fields or blank dates in the **Comments** section. Place an ☒ in appropriate boxes. Circle AMENDED items in red.

**VITAL STATUS**Vital Status: ☐ Alive ☐ Dead Date of last contact or death:  /  / 

If vital status is Dead, complete and submit Notice of Death form.

**DISEASE FOLLOW UP STATUS**

Has the patient had a documented clinical assessment for this cancer (since submission of the previous follow-up form)?

☐ No ☐ Yes If Yes, Date of Last Clinical Assessment:  /  / **NOTICE OF FIRST RELAPSE OR PROGRESSION**

Has the patient developed a first relapse or progression that has not been previously reported?

☐ No ☐ Yes If Yes, Date of Relapse or Progression:  /  / 

Site(s) of Relapse or Progression: \_\_\_\_\_

**NOTICE OF NEW PRIMARY**

Has a new primary cancer or MDS (myelodysplastic syndrome) been diagnosed that has not been previously reported?

☐ No ☐ Yes If Yes, Date of Diagnosis:  /  / 

New Primary Site: \_\_\_\_\_

**NON-PROTOCOL TREATMENT**

Has the patient received any non-protocol cancer therapy (prior to progression/relapse) not previously reported?

☐ No ☐ Yes If Yes, Date of First Non-Protocol Therapy:  /  / 

Agent Name(s): \_\_\_\_\_

**LONG TERM ADVERSE EVENT**Has the patient experienced (prior to treatment for progression or relapse or a second primary, and prior to non-protocol treatment) any severe (grade  $\geq 3$ ) long term toxicity that has not been previously reported?☐ No ☐ Yes If Yes, Adverse Events and Grades: \_\_\_\_\_**Comments:**

64587

9/15/2003

[figure not shown]

# SWOG NOTICE OF DEATH

Page 1 of 1

SWOG Patient ID

Most Recent SWOG Study No. S

Patient Initials \_\_\_\_\_ (L, F M)

Institution / Affiliate \_\_\_\_\_ Physician \_\_\_\_\_

Participating Group: Group Name/Study No./Patient ID \_\_\_\_\_ / \_\_\_\_\_ / \_\_\_\_\_

**Instructions:** Answer all questions and explain any blank fields or blank dates in the **Comments** section.

Place an ☒ in appropriate boxes. Circle **AMENDED** items in red.

Date of Death:  /  /  (month / day / year)

## CAUSES OF DEATH

**Any cancer (select one):**

☐ No ☐ Primary Cause ☐ Contributory ☐ Possible ☐ Unknown

**If cancer was the primary cause or if cancer possibly or definitely contributed to death, and the patient had had multiple tumor types, specify those which were causes of death:**

☐ Cancer of most recent SWOG study, specify cancer: \_\_\_\_\_

☐ Cancer of other SWOG study, specify cancer: \_\_\_\_\_

☐ Other cancer, specify: \_\_\_\_\_

**Toxicity from disease related treatment (select one):**

☐ No ☐ Primary Cause ☐ Contributory ☐ Possible ☐ Unknown

**If Primary Cause, Contributory or Possible, specify treatment and toxicity:**

**Non-cancer and non-treatment related causes (select one):**

☐ No ☐ Primary Cause ☐ Contributory ☐ Possible ☐ Unknown

**If Primary Cause, Contributory or Possible, specify:**

**Autopsy?** ☐ No ☐ Yes ☐ Unknown

**Source(s) of death information:**

- ☐ Autopsy report  
☐ Medical record / Death certificate  
☐ Physician  
☐ Relative or friend  
☐ Other, specify: \_\_\_\_\_

**Comments:**

49467

9/1/2003

[figure not shown]

## 19.1 Acupuncture Description and Side Effects

### Description of True Acupuncture

The true acupuncture protocol and procedures employed will be devised with adherence to the Standards for Reporting of Controlled Trials in Acupuncture (STRICTA) recommendations. The acupuncture protocol was selected based on a standard Traditional Chinese Medicine (TCM) point prescription and informal practitioner query. A manualized protocol (*i.e.*, a protocol that is standardized but allows the Study Acupuncturist to modify treatments based on the patient's current joint symptoms) has been developed. The manualized protocol was selected as opposed to a fixed acupuncture point protocol to facilitate the systematic delivery of standardized acupuncture treatments and because it was shown to be effective in other acupuncture trials. (79,80,96,143,150) Patients will be scheduled for twice weekly 45-minute acupuncture sessions (30-minute acupuncture, 15-minute set-up) for 6 weeks (8-12 sessions) followed by 6 weekly treatments (4-6 sessions) for maintenance (12-18 sessions total over 12 weeks). The true acupuncture protocol includes standardized body and auricular treatments (Table 1). This point prescription is based on a standard TCM point prescription to treat "Bi Syndrome" and the National Acupuncture Detoxification Association (NADA) protocol applied to one ear to relieve pain and decrease stress. At every acupuncture visit, the patients assigned to true acupuncture will receive the full body acupuncture prescription and the auricular acupuncture-NADA protocol in one ear (to be alternated at each visit). (151) In addition, each session will include a joint-specific point prescription tailored to up to four of the patient's most painful joints, including knees, fingers, lumbar area, shoulders, hips, and wrists. (79, 144) The anatomic site selection may vary between visits depending on the patient's current symptoms.

Acupuncture needles used will be Mac™ single-use, sterile, and disposable. The full body acupuncture needles will be 1 inch, 1.5 inches or 3 inches and 34-gauge (manufactured by Tian Jin Haing Lin Sou Won Medical Instrument Co., Ltd; distributed by Mac Co., Roslyn Heights, New York, USA) and auricular needles will be 15mm and 38-gauge (Seirin-America, Inc., MA). The needling protocol will consist of first swabbing all points with alcohol and needling auricular points, then needling full-body points. The needles will be inserted to the proper needling depth as determined by standard point locations and to elicit a *de qi* sensation at all standardized full body acupuncture points. (152) The needles will remain *in situ* for 20-25 minutes during which the Study Acupuncturist will return to stimulate the needles once, utilizing even needle technique in order to re-elicited the *de qi* sensation. If needed, to access joint-specific points that are not accessible in the supine position, needles may be inserted after the first set, at the proper depth and angle, eliciting a *de qi* sensation, and retained for 10 minutes. No electrical stimulation will be used. One licensed Study Acupuncturist will perform all treatments. In addition, up to 2 licensed acupuncturists will be trained in administering the protocol in the event of schedule conflicts. At 6, 12, 24, and 52 weeks, to assess the adequacy of blinding, patients will give an opinion about their treatment assignment. After the 24-week visit, patients will receive a voucher for 10 free acupuncture sessions to be administered by the study acupuncturist(s) used off-study at her convenience. Any additional acupuncture treatments received off-study will be recorded at 24 and 52 weeks. All of this information will be recorded on the **S1200** Assessment of Blinding Form (Form #20574).

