### Description of Sham Acupuncture

The sham acupuncture intervention, which is a control for acupoint specificity, will use superficial needle insertion at body locations not recognized as true acupoints. Similar to the true acupuncture arm, patients will be scheduled for twice weekly 45-minute acupuncture sessions (30-minute sham acupuncture, 15-minute set-up) for 6 weeks (8-12 sessions) followed by 6 weekly treatments (4-6 sessions) for maintenance (12-18 sessions total over 12 weeks). The sham acupuncture protocol includes full body and joint-specific treatments and an auricular sham intervention (Table 2). At every acupuncture visit, the patients assigned to sham acupuncture will receive the full body sham and auricular sham acupuncture prescriptions. In addition, each session will include a joint-specific sham point prescription tailored to up to four of the patient's most painful joints, including knees, fingers, lumbar area, shoulders, hips, and wrists. The anatomic site selection may vary between visits depending on the patient's current symptoms.

Acupuncture needles used will be Mac™ single-use, sterile, and disposable with plastic guide tube. The sham acupuncture needles will be 0.5 inch 34-gauge (manufactured by Tian Jinhaing Lin Sou Won Medical Instrument Co., Ltd; distributed by Mac Co., Roslyn Heights, New York, USA). The needling protocol will consist of first swabbing all points with alcohol and needling full body and joint-specific sham points, inserting the needle by tapping in just to the upper level of the guide tube, at a transverse angle. The auricular

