sham procedure will include application of 3 adhesives to selected points on the ear (Table 2). The auricular adhesives are latex-free and will be loosely attached and pressed to the sham points on the helix of the auricle. The needles and auricular adhesives will remain in situ for 20-25 minutes during which the Study Acupuncturist will return to check the patient and lightly touch each needle handle and auricular adhesive in order to mimic the true intervention. No electrical stimulation will be used. The same Study Acupuncturists will administer both the true and sham acupuncture interventions. At 24 weeks, to assess the adequacy of blinding, patients will give an opinion about their treatment assignment. After the 24-week visit, patients will receive a voucher for 10 free true acupuncture sessions to be administered by the study acupuncturist(s) and used off-study at her convenience. Any additional acupuncture treatments received off study will be recorded at 24 and 52 weeks. All of this information will be recorded on the **S1200** Assessment of Blinding and Additional Acupuncture Form (Form #20574).

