| A Sham 1                                                                                                                 | On the helix of the auricle between helix point #5 and #6                                                                                                               |
| A Sham 2                                                                                                                 | On the helix of the auricle between helix point #4 and #3                                                                                                               |
| A Sham 3                                                                                                                 | On the helix of the auricle between the ear apex and helix point #1                                                                                                     |
| Joint-specific sham point protocols (tailored to up to 3 of the patient's most painful areas with each treatment) |                                                                                                                                                                         |
| Knee                                                                                                                     | 2 cun above sham 3 or 4, respectively                                                                                                                                   |
| Fingers/ Wrist                                                                                                           | On the lateral side of the left and right forearm, near the elbow, 5 cun below the olecranon, 0.5 cun toward the anterior of the small intestine meridian               |
| Lumbar                                                                                                                   | On the back at the level of thoracic vertebra 8, 5 cun from the center of the spine, 2 cun from the outer channel of the urinary bladder meridian (needled bilaterally) |
| Shoulder                                                                                                                 | On the lateral side of the left and right arm, above the elbow, 3 cun above the olecranon, 0.5 cun toward the anterior of the small intestine meridian                  |

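### Only the true arm has an optional second needle set for points not reachable supine, so sessions that use it differ from sham by 10 minutes of needle retention and an extra round of handling

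*Protocol*

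**What the plan says.** All of the relevant text is in Protocol Appendix 19.1.

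**True arm.** Sessions are planned as "45-minute acupuncture sessions (30-minute acupuncture, 15-minute set-up"). The first needles stay in "for 20-25 minutes during which the Study Acupuncturist will return to stimulate the needles once". The text then adds: "If needed, to access joint-specific points that are not accessible in the supine position, needles may be inserted after the first set". These further needles are placed to elicit *de qi* "and retained for 10 minutes".

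**Sham arm.** The planned session has the same 30 + 15 minute split. Needling is described as one step, "needling full body and joint-specific sham points, inserting the needle by tapping in just to the upper level of the guide tube", followed by one retention period: "The needles and auricular adhesives will remain in situ for 20-25 minutes during which the Study Acupuncturist will return to check the patient". During that period the acupuncturist lightly touches the needle handles and ear adhesives, with the stated aim of imitating the true procedure. No second set, change of position or further retention is described.

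**Point tables.** Both arms tailor needling to the most painful joints, including the lumbar area. The true lumbar points in Table 1 are on the back. The sham lumbar point in Table 2 is too: "On the back at the level of thoracic vertebra 8, 5 cun from the center of the spine", needled on both sides.

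**The concern.** True versus sham is one of the two primary comparisons, each tested at two-sided 0.025 (Section 11.1). Patients are meant to be blind to which of the two they receive (Section 7.6a). The endpoint is a self-reported worst-pain score, which can respond to contact and handling as well as to needling. The Background itself cites placebo responses of 25-55% for shams of this type.

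If both descriptions are followed as written, some true-arm patients get a second round of needling, implicitly a change of position, more practitioner contact and a longer time with needles in. Sham patients whose back point needs the same access get no described counterpart. Part of any observed difference could then reflect these extras and not the acupuncture points or the needling technique.

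The Activation Revision (item 26) records that the sentence was added to the true-arm text, and lists edits to the sham text without a counterpart. That fits an oversight but does not prove one.

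**Working it through.** The plan gives no total retention figure to reproduce. The check adds the stated times and compares the two texts.

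**Inputs (Appendix 19.1).** True first set 20-25 min; true second set, if used, 10 min; sham retention 20-25 min; planned treatment 30 min plus 15 min set-up in both arms. Section 7.6a gives 8-12 sessions in the first 6 weeks.

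**Retention per session**
- True, no second set: 20-25 min.
- True, second set used: 20 + 10 = 30 to 25 + 10 = 35 min.
- Sham: 20-25 min in every session.
- Difference when the second set is used: 10 min. Relative to a single set: 10/25 = 40% to 10/20 = 50%.

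**Against the stated treatment time**
- 30 - 30 = 0 and 35 - 30 = 5, so the two true-arm phases exceed the 30 minutes by 0-5 min, before any time to reposition the patient and insert the second set.
- With the full set-up: 15 + 30 = 45 to 15 + 35 = 50 min. The session fits the 45-minute booking at the lower end, or if set-up takes less than its allowance.

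**Over the primary treatment period.** If *p* is the share of true-arm sessions using the second set, the average excess is 10 × *p* min per session. The protocol does not give *p*, so the average can lie anywhere from 0 (*p* = 0) to 10 min (*p* = 1). The ceiling by week 6 is 8 × 10 = 80 to 12 × 10 = 120 min, for a patient who has a second set at every session. Joint selection may vary between visits, so this is an upper bound and not an expectation.

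**When the step would arise, from Tables 1 and 2**

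| Joint | True points | Sham point |
|---|---|---|
| Lumbar | Spine and beside it, on the back | Back, T8 level, both sides |
| Shoulder | Two of three are posterior (SJ-14, SI-10) | Lateral upper arm |
| Hip | One lies between the greater trochanter and the sacrum (GB-30) | Thigh |

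The lumbar row needs access to the back in both arms, but only the true text provides a step for it. By location, shoulder and hip may also call for the step in the true arm and not in the sham arm. The protocol does not list which points it regards as unreachable supine, so this is inferred from the anatomy.

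**The case against.** Several counter-arguments have force.

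- **The arms differ by design.** The sham is described as a control for point specificity. Depth, *de qi*, ear needles versus adhesives, needle length and number of points already differ, and equal retention minutes are not a stated aim. Needles placed with *de qi* at joint-specific points are part of the treatment under test. This stands in part: not all of the extra 10 minutes is non-specific. The extra round of handling and contact is not point specificity, however, and the sham text does aim to imitate handling.
- **A reader might infer that true-arm visits are longer.** The documents do not say so. Both arms are booked for 45 minutes with the same acupuncturists.
- **A reader might infer that the sham cannot be delivered as written.** The sham text fixes no position, so needling the back in another position would not breach it. The gap is a missing counterpart and not an internal contradiction.
- **A reader might infer that sites will each improvise a different sham.** Section 15.3 and Appendix 19.4 provide a manual, video, observed practice of both procedures, quality checks and monthly calls. The manual is not shown and may cover the point.
- **A reader might infer that the difference could never be examined afterwards.** Section 7.6b records the point prescription at every visit, so sessions with back points can be identified. Section 11.2d compares patients' guesses about assignment. Neither shows whether a second set was used.

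The step is also optional, and the change of position is implied and not stated.

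**Conclusion.** The point holds in a limited form. In sessions where the second set is used, the protocol gives the true arm 10 more minutes of stated needle retention (30-35 against 20-25) and an additional round of needling and handling. The sham description has no counterpart even for its own back point. Booked visit length is equal.

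This could bias one of the two primary comparisons on a patient-reported endpoint, most plausibly in favour of true acupuncture. Its size cannot be stated: the share of affected sessions is not given, and nothing in the document converts minutes or handling into points on the pain scale. A figure for the arm-wide average excess would need an assumed share for which the protocol offers no basis. The Background names lower back, hips and shoulders among the usual sites, but reports hand and/or knee symptoms in over half of affected women.

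Separately, the true-arm phases agree with the stated 30-minute treatment only at the lower end. The conclusion rests on reading the two descriptions as written, without the training manual. It should be corrected, but it does not invalidate the design.

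**What to change.** Reconcile the true and sham descriptions and Tables 1 and 2 in Appendix 19.1, so that the session steps and retention time for points not reachable supine are matched between the two needling arms. Make the stated treatment time agree with the sum of the phases. Which procedure to adopt is for the sponsor to decide.

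Carry the reconciled text into the training manual and online module. Add an item to the acupuncture e-CRF recording at each visit, in both needling arms, whether a second set was used. The frequency of the step can then be reported by arm and its influence examined alongside the point prescriptions already collected.

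The cost is about one paragraph of protocol text, a manual update and one e-CRF item. Depending on the procedure chosen, some sessions may involve slightly more handling. By the arithmetic above, that stays within the 45-minute visit only at the lower end of the range or if set-up takes less than its 15 minutes, so the time statement should be settled in the same edit.
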